**Methods:**

This will be a two group, parallel randomized controlled trial design, with single assessor blinding. Thirty healthy runners will be recruited to participate in a six weeks neuromuscular training program. Participants will be randomized into either a generic training group, or a biomechanically informed training group. Primary outcomes include self-determined running velocity with a 20 % body weight load, jump power, hopping leg stiffness, knee extensor and triceps-surae strength. Secondary outcomes include running kinetics and kinematics. Assessments will occur at baseline and post-training.

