### Sample size calculation

This study was powered on the effects of a core stability program on changes to hopping leg stiffness [26]. Sample size was planned based on a two way, repeated measures ANOVA, using the Hotelling-Lawley Trace to test for an intervention by time interaction [27]. Previous studies on leg stiffness reported a standard deviation of 3600 N/m [26], and a correlation between repeated measures of 0.80 [28]. For a desired power of 0.80, and a Type 1 error rate of 0.05, 24 participants are needed to detect a between group mean difference of 3000 N/m. In order to account for a 20 % dropout over the six week intervention period, 30 participants will be tested.

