### Intervention

#### Familiarization phase (all participants) (two weeks)

All participants will first be enrolled into a two week preparatory training phase prior to baseline testing and randomization. During this phase, all participants will perform the same set of exercises (see Additional file 1 ‘Familiarization phase’). This preparatory phase will control for the effect of motor learning on improvements in performance on the assessments [45–47]. Participants will be encouraged not to alter any of their personal training regimes throughout the entire program. Self-reported training for the period of the intervention will be recorded by the participants in a supplemented training diary log book. Variables to report for self-resistance training include external mass magnitude, sets, and repetitions. Variables to report for cardiovascular training include duration, and type of exercise undertaken.

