Descriptive statistics (mean and standard deviation) will be calculated for baseline demographics of participants. Between groups difference in baseline demographics will be calculated using *t*-test or non-parametric test where appropriate. Analysis will be based on an intention-to-treat (ITT) using the multiple imputation method [62]. A repeated measures linear mixed model with time, group, and their interaction as fixed effects, and participants clustered within groups as random effects will be used to analyse our discrete dependent variables [63]. For the linear mixed model, significance will be set at α = 0.05. Descriptive statistics and linear mixed modelling will be performed in R software within RStudio (Version 0.98.1062, RStudio, Inc.). Statistical testing between group and within group mechanical wave form data (kinematics, kinetics) will be analysed using Statistical Parametric Mapping (SPM). Statistical significance will be inferred using Random Field Theory (RFT), with appropriate Bonferroni correction applied to retain a family-wise error rate of α = 0.05. SPM will be performed using the latest version of spm1d package (www.spm1d.org), installed in Python 2.7, and implemented in Enthought Canopy 1.5.4 (Enthought Inc., Austin, USA).

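### The planned group × time interaction is a change-score contrast; adjusting for the baseline already collected would be modestly more precise at almost no cost

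*Protocol article*

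**What the plan says.** The section Dependent variables and statistics of the protocol article analyses the discrete outcomes by a repeated measures mixed model "with time, group, and their interaction as fixed effects, and participants clustered within groups as random effects", at α = 0.05, under intention to treat with multiple imputation. It names no baseline covariate and does not constrain the two groups to a common baseline mean.

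The abstract gives two measurement times: "Assessments will occur at baseline and post-training". The Sample size calculation is built on the same effect, "using the Hotelling-Lawley Trace to test for an intervention by time interaction", and the Objectives speak of comparing changes between the two programs.

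The familiarization section places the two-week preparatory phase "prior to baseline testing and randomization". I read this as baseline testing first and randomization second.

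**The concern.** In the planned model the group term is free at baseline, so each arm gets its own baseline mean. If baseline is measured before randomization, the two true means are equal by design and any observed difference is chance. Estimating them separately discards that knowledge.

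The interaction then subtracts the whole observed baseline difference. When the pre/post correlation ρ is below 1, only a fraction ρ of that difference is expected to persist to post-training, so the subtraction over-corrects. Allocation is stratified by gender only, so nothing in the design balances the baseline values of the outcomes, and with 12 to 15 per arm visible imbalance is likely. At stake are some precision in a small trial and an estimate that moves with the luck of the baseline draw.

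**Working it through.** **Inputs.** All come from the Sample size calculation. The SD for leg stiffness is 3600 N/m. The association between the two assessments is given as "a correlation between repeated measures of 0.80". Target power is 0.80 and α is 0.05. The result reported there is "24 participants are needed to detect a between group mean difference of 3000 N/m". Dropout is 20 %, giving 30 recruited. Allocation is 1:1. The sidedness of the test is not stated; I take it as two-sided, since the Hotelling-Lawley test is an F-type test.

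**Reproducing the plan's figure.** With two groups and two times, the Hotelling-Lawley test of the interaction is a two-sample t-test on change.

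- SD of change = 3600 × √(2(1 − 0.80)) = 2276.8 N/m.
- Noncentral t: 11 per arm, 22 in total, against 24 stated. That is close enough to confirm that a change-score calculation was done.
- 24 / 0.80 = 30, as stated.
- Power with 12 per arm: 0.87.

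**The planned effect is the change score.** In simulated complete data with two times, the group × time coefficient and standard error from the planned model were identical to those of the difference in mean change (0.8903, SE 0.2620).

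**Baseline-adjusted alternative, large-sample formula.**

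- Residual SD = 3600 × √(1 − 0.80²) = 2160 N/m.
- Variance ratio, adjusted to change = (1 − ρ²) / (2(1 − ρ)) = (1 + ρ)/2 = 0.90 at ρ = 0.80.

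**Small-sample correction.** The formula treats the baseline slope as known. Estimating it from 2n participants multiplies the variance by about 1 + 1/(2n − 4). With n = 12 this is 1.05, so the ratio is 0.90 × 1.05 = 0.945. With n = 15 it is 1 + 1/26, so the ratio is 0.935. Simulation agrees (about 0.94 and 0.93). Simulated type I error was between 0.047 and 0.048 for both analyses.

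**Power with 12 per arm** for a standardised effect of 3000/3600 = 0.83. Only the 0.80 row uses a correlation from the document; the other rows are assumptions shown as a range. The ratio is (1 + ρ)/2 × 1.05, and the adjusted power is simulated with the slope estimated.

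| ρ | Variance ratio | Power, change | Power, adjusted |
|---|---|---|---|
| 0.50 | 0.79 | 0.50 | about 0.60 |
| 0.60 | 0.84 | 0.59 | about 0.66 |
| 0.70 | 0.89 | 0.71 | about 0.76 |
| 0.80 | 0.945 | 0.87 | about 0.89 |
| 0.90 | 1.00 | 0.99 | 0.99 |
| 0.95 | 1.02 | 1.00 | 1.00 |

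With 15 per arm and ρ = 0.80, power is 0.94 against 0.95.

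**Sensitivity to imbalance.** Given an observed baseline difference d, the expected change-score estimate is off by (1 − ρ)d. One standard error of the baseline difference with 12 per arm is 3600 × √(2/12) ≈ 1470 N/m. The shift is then 0.20 × 1470 = 294 N/m at ρ = 0.80 (10 % of 3000 N/m), and 0.50 × 1470 = 735 N/m at an assumed ρ of 0.50 (about 24 %).

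**The case against.** The strongest reply is that nothing here is wrong. The objective is to compare changes, the trial is powered on the interaction, and the analysis tests that interaction. The test holds its size and, on the stated inputs, exceeds its 0.80 target. All of that stands. So does the point that the gain for leg stiffness, the only outcome with documented inputs, is under 2 power points.

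It could also be said that a condensed article leaves covariates to an analysis plan. That carries less weight, because the article states the fixed effects of the model and the choice follows from them. Adjustment would still answer the objective: with baseline as covariate, analysing the post-training value or the change gives the same group effect.

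A reader might infer more than the documents support:

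- *That the planned estimate is biased.* It is unbiased over randomizations, and its standard error already includes chance baseline variation. The shift shown above is conditional on the imbalance that happens to occur.
- *That the gain at ρ = 0.80 is the formula's 10 % of variance and power of 0.90.* This ignores the cost of estimating the slope from 24 people.
- *That adjustment can never lose.* This is a large-sample result. With 12 per arm the advantage is gone at about ρ = 0.90, and the variance is 2 to 3 % larger at about 0.95.
- *That the other primary outcomes are underpowered.* The article gives no correlations or target effects for them. The familiarization phase and the repeated trials may well keep their correlations high.
- *That a group-level random effect is being fitted beside a fixed group effect.* The phrase about participants clustered within groups most naturally means a participant intercept, and no group-level variance is stated.

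**Conclusion.** The point holds as one of efficiency and robustness, not validity. The protocol fixes an unconstrained interaction where a better use of the same baseline is available by design. On its own inputs with 12 per arm, the gain is a variance ratio of about 0.94 and power of about 0.89 instead of 0.87. For the same standardised effect it would be about 5 power points at ρ = 0.70, 7 at 0.60 and 10 at 0.50, but these lower correlations are assumptions. At 0.90 or above there is nothing to gain.

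The conclusion rests on baseline being measured before allocation, as the familiarization section implies; on equal variances at the two times; and on complete or imputed pairs, for which the interaction equals the change score exactly. Because the change is nearly free and the trial is small, it is worth making.

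**What to change.** State that the primary estimate for each discrete outcome is the group difference at post-training, adjusted for the baseline value of the same outcome (ANCOVA), fitted on each imputed data set and then pooled. Equivalently in aim, keep the mixed model but constrain the two groups to one baseline mean, by dropping the group main effect and keeping time and group × time. The interaction as now written can be reported as a supporting analysis.

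The sample size needs no change: by the same noncentral t calculation, the planned analysis needs 22 evaluable participants and 24 are planned. The cost is a change of analysis wording, one degree of freedom and the small variance penalty for estimating the baseline slope. No new data or participants are needed.

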## Discussion

Carrying some form of external load is becoming increasingly ubiquitous in running related sports, such as adventure racing and ultra-endurance events. Running mechanics alterations with load carriage could represent adaptive or mal-adaptive mechanics. Mechanical changes like increased joint power may represent attempts at maintaining constant running velocity, support an increased weight, maintain postural control and/or attenuate excessive impact shocks. In addition, some mechanical changes are likely to represent a failed capacity of lower limb muscles to cope with the additional load, that result in a reduction in running performance and an increased risk of future injuries. The long term sequela not only has an effect at an individual level, but could affect long term sporting participation and health care costs. In addition, runners may have to compromise running economy and running velocity when load carriage is involved if lower limb muscles are not tuned to the specific neuromuscular demands. Velocity decrements as a result of load carriage would result in compromised survivability in combat soldiers, and reduced performance in competing running athletes. This study will provide preliminary evidence of the potential efficacy of a targeted neuromuscular training program or a best-practice strength training program on improvements in strength, stiffness, running velocity and biomechanics during load carriage running.

## Abbreviations

AF: Augmented feedback
BW: Body weight
CMJ: Countermovement jumps
CONSORT: Consolidated Standards of reporting trials
GRF: Ground reaction force
KP: Knowledge of performance
RM: Repetition maximum
RRI: Running related injuries
SJ: Squat jumps
SL hop: Single leg vertical hoping
